## Section G: Sample Size/Data Analysis

### G1. Sample Size

How many subjects (or specimens, or charts) will be used in this study?

Local: 40      Worldwide: 40

Please indicate why you chose the sample size proposed:

This will be a pilot study, and we have done a power analysis for differences in our study based on the preclinical studies done on rabbits in which studies with lavaged, sedated juvenile rabbits weighing around 1000 g were assessed for work of breathing, estimated as pressure x rate products (PRPs) comparing standard bubble nasal Bn-CPAP with Seattle-PAP, the difference in the means for PRPs in the n=12 rabbits studied was 148.24 cmH2O/min. The standard deviation of the differences, in the paired comparisons of Bn-CPAP vs. 135 degree Seattle-PAP, was 154.23. Sample size calculations for two-tailed alpha 0.05 gave n=11 and 14 for powers of 0.80 and 0.90, respectively. To allow for anticipated greater heterogeneity of the human infant population that we need to characterize, we propose to study 40 infants, with ongoing review of accumulating data by a qualified person not otherwise involved in the study.

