### G2. Data Analysis

Provide a description of your plan for data analysis. State the types of comparisons you plan (e.g. comparison of means, comparison of proportions, regressions, analysis of variance). Which is the PRIMARY comparison/analysis? How will the analyses proposed relate to the primary purposes of your study?

The PRIMARY comparison will be work of breathing, as estimated by pressure-rate products, assessed in each patient in each of the three periods, the first being on standard Bn-CPAP, using the Fisher-Paykel bubble CPAP device. The second study period will be with Seattle-PAP, and the third period will be with return of the patient to FP-Bn-CPAP for characterization.

The primary outcome variable is work of breathing (WOB) over a two hour period, estimated from pressure-rate products, which are assessed with 6 Fr (2 mm) catheters placed in the distal esophagus for monitoring esophageal pressures (Pes), thereby estimating changes in pleural pressures during breath cycles. The following endpoints would also be assessed: Oxygen saturations and Fraction of Inspired Oxygen (FiO2) needed to keep saturations in acceptable ranges, Heart Rates (HR), transcutaneous carbon dioxide (TcPCO2), and respiratory rates throughout the 6 hour study period. The primary outcome measure will be evaluated during the last 15 minutes of each 2 hour study period. If the subject needs clinical interventions during this period, the closest preceding 15 minutes will be used for analysis.

The pressure-rate product (PRP) data will be assessed statistically by paired t-tests, with Bonferroni corrections for multiple comparisons. Lacking any relevant human data, we estimate sample size requirements from our preclinical data, obtained in studies with juvenile rabbits. These rabbits were of one sex, relatively homogeneous genetic background, and were not born prematurely, but data estimates of differences in means and SDs of differences, with a power of 0.9, indicates 17 subjects are needed, with alpha 0.05.

Also, the study plans are to use video recording of the infants' breathing motions to test the hypothesis that methods of assessments of those recorded breathing motions can be correlated with measured PRPs to identify a method of producing objective assessments of work of breathing from video clips.

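### Optional improvement, not an error: Holm's step-down correction could replace the valid Bonferroni correction of the paired PRP tests in G2, with some gain in power if the human effect is well below the rabbit effect

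*Protocol*

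**What the plan says.** Section G2 makes PRP the primary comparison, "assessed in each patient in each of the three periods": first on the Fisher-Paykel (F&P) device, then on Seattle-PAP, then on F&P again. The role given to the last period is that "the third period will be with return of the patient to FP-Bn-CPAP for characterization". The data are to be compared by paired t-tests, "with Bonferroni corrections for multiple comparisons". G2 does not say how many comparisons are in the family. It also does not say whether a single-step or a step-down form is meant, but Bonferroni without qualification ordinarily means the single-step form.

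The planning figures come from rabbits. In G1, "the difference in the means for PRPs in the n=12 rabbits studied was 148.24" cmH2O/min, and the SD of the differences, "in the paired comparisons of Bn-CPAP vs. 135 degree Seattle-PAP, was 154.23". G1 states: "Sample size calculations for two-tailed alpha 0.05 gave n=11 and 14 for powers of 0.80 and 0.90, respectively". G2 repeats the exercise and, "with a power of 0.9, indicates 17 subjects are needed, with alpha 0.05". The planned enrolment is 40, justified in G1 by the greater heterogeneity expected in human infants.

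**The concern.** With two comparisons, single-step Bonferroni holds each test to 0.05/2 = 0.025 even after the other has been rejected. Holm's method holds only the smaller p-value to 0.025. Once that is rejected, the other is tested at 0.05. The t-tests, assumptions and familywise error are the same.

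What is at stake is the second comparison. The two methods differ only when the smaller p-value is at most 0.025 and the larger lies between 0.025 and 0.05. A real device effect could then be reported as shown against one F&P period and not against the other, although a method with the same error control would have confirmed both. The chance of at least one significant comparison is identical under the two methods.

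**Working it through.** **1. Holm's error control with two tests.** If both null hypotheses are true, a false rejection needs the smaller p-value to be at most 0.025, which has probability at most 2 × 0.025 = 0.05. If only one is true, a false rejection needs its own p-value to be at most 0.05. The familywise error is at most 0.05 in either case, as for Bonferroni.

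**2. The protocol's own sample sizes.** The standardised effect is 148.24/154.23 = 0.961. The power of a two-sided paired t-test is P(|T| > t(1 − α/2, n − 1)), where T is noncentral t with n − 1 degrees of freedom and noncentrality 0.961 × √n.

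- α = 0.05 needs n = 11 for power 0.80 and n = 14 for power 0.90 (0.913 at 14). Both G1 figures reproduce.
- α = 0.05/2 = 0.025 needs n = 17 for power 0.90 (0.919 at 17). This is the G2 figure.
- α = 0.05/3 gives 0.886 at 17, so n = 18 is needed.

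The 17 in G2 therefore fits Bonferroni for two comparisons. The protocol does not say that this is how it was obtained.

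**3. Bonferroni against Holm at n = 40.** Simulation, with 40,000 to 60,000 trials per setting. Assumptions: normal errors, equal and independent between periods within an infant (so the two Seattle-versus-F&P differences correlate 0.5), with no drift and no carry-over. The effect is in SDs of the paired difference.

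Probability that both comparisons are significant, two-comparison family:

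| Effect (SD) | Share of rabbit effect | Bonferroni | Holm | Gain (points) |
|---|---|---|---|---|
| 0.40 | 0.40/0.961 = 42% | 42% | 53% | 11 |
| 0.45 | 0.45/0.961 = 47% | 55% | 66% | 11 |
| 0.50 | 0.50/0.961 = 52% | 68% | 78% | 10 |
| 0.58 | 0.58/0.961 = 60% | 84% | 90% | 6 |
| 0.961 | 100% | 99.97% | at least 99.99% | at most 0.03 |

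Repeat runs differ by up to about one point in the first four rows (Bonferroni at 0.40 SD came out at 41% or 42%).

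Probability that one given Seattle-versus-F&P comparison is significant, same family:

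- 40% of the rabbit effect: 54.5% against 60.3%, a gain of 5.8 points.
- 50%: 75.6% against 80.9%, a gain of 5.3 points.
- 60%: 90.1% against 93.4%, a gain of 3.3 points.

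**4. If all three pairs of periods are tested.** The hypotheses are then logically linked: if one equality among three means is false, at most one other can be true. Shaffer's step-down may therefore test the smallest p-value at 0.05/3 = 0.0167 and the other two at 0.05. At 0.40 / 0.45 / 0.50 / 0.58 SD, the chance that both Seattle-versus-F&P comparisons are significant is 35 / 47 / 61 / 79% with Bonferroni, 41 / 55 / 67 / 84% with Holm and 51 / 64 / 76 / 90% with Shaffer. At the rabbit effect, Bonferroni gives 99.96% and Holm 99.98%.

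**The case against.** The case for leaving G2 alone is strong in several respects.

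- **Bonferroni is valid and prespecified.** A reader might infer that G2 contains an error. It does not: the method controls the familywise error and conflicts with no other section. The statistical analysis plan, not available here, may also refine it. This stands.
- **There is no loss on the protocol's own inputs.** At 0.961 SD and 40 infants the gain is at most 0.03 points. The cost of the correction also appears to be covered already, since 17 subjects fit a two-comparison Bonferroni and 40 are planned. This stands for the rabbit effect. It does not settle the matter, because G2 says relevant human data are lacking and G1 expects more heterogeneity in infants, which would shrink the standardised effect. How far is not stated.
- **Success on both comparisons is not a stated aim.** A reader might take the third period as a reversal that must be significant. G2 gives it only a descriptive role, and no section makes a significant reversal a condition of success. If both were required, each could be tested at the full 0.05 and no correction would be needed. The gain for one given comparison does not depend on such a rule, but it is smaller.
- **The larger gains need a less likely reading.** Differences of up to 64 − 47 = 17 points arise only with Shaffer's procedure and three pairwise tests, whereas the 17 subjects in G2 point to two comparisons.
- **The power is not given up for nothing.** Bonferroni supplies simple simultaneous confidence intervals, which are useful in a pilot study. Holm does not. This stands and limits how strongly the change can be urged.

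**Conclusion.** This is a cheap improvement to a valid method. For as long as more than one paired test is kept, Holm is never less powerful than Bonferroni at the same familywise error. With 40 infants and two Seattle-versus-F&P comparisons, the benefit is negligible at the rabbit effect. If the human effect is about 0.40 to 0.58 SD, it is about 6 to 11 points for both comparisons and about 3 to 6 points for one given comparison. That effect range is an assumption, as are the equal independent period errors and the absence of drift and carry-over. The documents do not support a claim that the trial is underpowered because of Bonferroni, or that its conclusion depends on the choice. The sponsor can reasonably decline if simultaneous intervals matter more to it than the second test.

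**What to change.** In G2, replace "with Bonferroni corrections for multiple comparisons" by: *with Holm step-down correction at familywise two-sided alpha 0.05*. If all three pairs of periods are to be tested, Shaffer's step-down is also valid and may be named instead (smallest p-value at 0.05/3, then the other two at 0.05). Make the change before the data are analysed.

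The t-tests, the data collected and the 40 infants stay as they are. To make up for the missing simultaneous intervals, report Bonferroni or ordinary 95% confidence intervals beside the Holm-adjusted p-values, and state which kind they are, because neither will always agree with the Holm decision.

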## Section H: Potential Risks/Discomforts

### H1. Potential Risks/Discomforts

Describe and assess any potential risks/discomforts and assess the likelihood and seriousness of such risks:

Standard adverse events in this patient population include mortality and complications of prematurity, which include bronchopulmonary dysplasia (BPD), intraventricular hemorrhage (IVH), retinopathy of prematurity and necrotizing enterocolitis (NEC). The inclusion criteria being stable and on nasal CPAP will minimize the possibility, but some of these infants will experience these adverse events as complications of prematurity.

Two hours of a different form of nasal CPAP is considered to be unlikely to be related to an increase in any of these adverse events. However, we will track and report these adverse events and they will be evaluated by [name] and/or Drs. [name] and [name]. These adverse events rarely are evident in the first 3 days of a stable patient, but they will be tracked and assessed by the investigators for 28 days after the study intervention day, and 36 weeks gestational age or discharge (whichever is earlier). At a biweekly meeting of investigators, including study respiratory therapists, the patients' data will be evaluated, and adverse events discussed. If in this patient population, adverse events accumulate at rates greater than in the general population of similar patients, we would stop the study and review possible mechanisms.

While placing an esophageal catheter is not a standard procedure in our nursery placing bigger, stiffer catheters for feeding and gastric decompression is routine and is done in all patients on nasal CPAP. OG tubes are placed after delivery and have to be replaced with some frequency as needed in premature infants with rare complications. Based on the experience we have with OG tubes we regard placement of an esophageal catheter for the 6 hour duration of the study as involving minimal risk. Risks include bleeding and esophageal perforation.

We do not expect to observe any complications or safety concerns with the device, as the interface between the device and the infant will be identical to those being used currently. Standard Bn-CPAP has been shown to be an efficacious method for respiratory support and the very rare complications primarily include:

1. Breakdown of the nasal area secondary to the interface of the baby with the device at the nose. This interface is identical in the two forms of nasal CPAP so, while we will record nasal breakdown we do not anticipate any differences between the two devices.
2. Pneumothorax: In randomized controlled trials of Bn-CPAP versus intubation and mechanical ventilation in the delivery room the development of pneumothorax was higher in the patients randomized to nasal CPAP than those randomized to intubation and mechanical ventilation. Our rates of pneumothorax in infants under 1500 grams is around 5%, and while we do not anticipate an increase in the pneumothorax rate in treated infants we will monitor this complication.

The primary risk factors for pneumothorax in premature infants is high levels of end pressure and nasal CPAP utilization in patients with hyaline membrane disease. We will not increase CPAP in this study, and the patients will be on less than or equal to 30% oxygen indicating that respiratory system function is good, so there is no foreseeable increased risk of pneumothorax.

[name], [name] and [name] will be notified of the development of a pneumothorax and review whether the pneumothorax can be attributed to the device. We would not stop the study after one event as in 20 infants 1 event would be 5%. If two events were encountered the study would be stopped and the data about mechanism for pneumothorax evaluated.

Lastly, potential loss of confidentiality is a risk.

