## Section F: Design/Procedure

### F1. Design

Select one category that most adequately describes your research:

i) Device, Phase I, Single Center

Discuss the research design including but not limited to such issues as: probability of group assignment, potential for subject to be randomized to placebo group, use of control subjects, etc.

This is a single site enrollment study with an enrollment target of 40 subjects. Texas Children's Hospital/Baylor College of Medicine will serve as the primary enrollment site.

Seattle Children's Hospital will provide Seattle-PAP and the comparator F&P BC 153-10 Bn-CPAP System (60 of each device). Seattle-PAP is provided under a 510(k) exemption; however, data may need to be submitted to US or international regulatory bodies in the future.

This is a pilot study in which each infant will serve as their own control. Study procedures will commence after informed consent is obtained and eligibility is confirmed. The study consists of 3 periods: (1) Bn-CPAP (~120 minutes) (2) Seattle-CPAP (~120 minutes) (3) Bn-CPAP (~ 120 minutes).

The subject's participation ends at the end of the 6 hour period. However, the study team will follow the subjects for targeted adverse events for 28 days from end of study AND 36 weeks gestational age OR discharge (whichever occurs first).

Inclusion Criteria:

1. Admitted to a bed at Pavilion for Women (or beds monitored by SickBay)
2. Less than or equal to 32 weeks gestational age
3. 6 to 72 hours of life (this parameter is chosen because this will be the time frame of subsequent non-inferiority trial).
4. Stable on standard bubble nasal CPAP (Bn-CPAP) defined as having less than 6 apneic spells per shift and requiring only tactile stimulation for treatment
5. On less than equal to 8 cm H2O on Bn-CPAP
6. Less than or equal to 30% oxygen requirement (this is chosen because if it is greater than 30% the patient is likely to have evolving hyaline membrane disease which is likely to dominate the serial measurements made and the effects of the device will be difficult to detect).
7. Informed Consent

Exclusion Criteria:

1. Congenital anomalies or suspected chromosomal abnormalities

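### The two-event pneumothorax stop is reasoned on 20 infants, but the trial enrols 40, where two events equal the protocol's own 5% background rate

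*Protocol*

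**What the plan says.** Section H1 gives the site's background: "Our rates of pneumothorax in infants under 1500 grams is around 5" per cent. It then sets the rule in two sentences. The first covers a single event: "We would not stop the study after one event as in 20 infants 1 event would be 5" per cent. The second covers the next one: "If two events were encountered the study would be stopped and the data about mechanism for pneumothorax evaluated". No effect of the device is expected: "we do not anticipate an increase in the pneumothorax rate in treated infants we will monitor this complication".

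The sample size is stated elsewhere. Section F1: "This is a single site enrollment study with an enrollment target of 40 subjects". Section G1: "we propose to study 40 infants, with ongoing review of accumulating data". Section G2 also ends its sample-size reasoning at 40. Every infant receives the device, because "This is a pilot study in which each infant will serve as their own control".

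For the other complications of prematurity, sections G2 and H1 use a different principle: the study stops if events accumulate faster than in comparable patients generally.

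The protocol does not tie the pneumothorax rule to the first 20 infants, to events attributed to the device, or to a stated period after the device is used. Section F1 says of follow-up that "the study team will follow the subjects for targeted adverse events for 28 days from end of study", with a further assessment at 36 weeks or discharge.

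**The concern.** The reason given for not stopping at one event is that the observed rate would equal the site's usual rate. That works for 20 infants. The trial plans 40, and the same reasoning then covers two events, which is the count that stops the study. The trigger is a fixed count that takes no account of how many infants have been studied, so a second event in the 40th infant has the same force as one in the 5th.

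At stake is whether those applying the rule know how often it would be triggered by background events alone. A low threshold in fragile neonates can be a deliberate choice. Here its only stated justification uses half the planned sample, so the protocol does not show that the false-halt risk at 40 was considered.

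**Working it through.** **Inputs.** Background rate p = 0.05 (H1, infants under 1500 g). Infants in the rule's reasoning: 20 (H1). Planned infants: 40 (F1, G1, G2). Trigger: 2 events (H1). Device effect: none (H1's expectation).

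**The protocol's own figure.** 1/20 = 0.05, so the stated 5% is reproduced.

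**The same reasoning at the planned size.** 2/40 = 0.05, the same 5%. By contrast, 2/20 = 0.10, twice the background. Expected events with a harmless device are 20 × 0.05 = 1.0 and 40 × 0.05 = 2.0. The second event is above background in 20 infants but equals it in 40.

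**Chance of reaching the trigger with no device effect.** Treat infants as independent with a common risk p. The trigger has been met by infant n if at least two of the first n have an event:

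P(X ≥ 2) = 1 − (1 − p)^n − n·p·(1 − p)^(n−1)

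- n = 20, p = 0.05: 1 − 0.3585 − 0.3774 = 0.264
- n = 40, p = 0.05: 1 − 0.1285 − 0.2706 = 0.601

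At 5% the probability first passes one half at the 34th infant (0.512).

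**Sensitivity to the background rate, n = 40.** The documents give no rate for the infants actually eligible, so rates other than 5% are assumptions.

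| True rate | P(at least 2 events in 40) |
|---|---|
| 1% | 6.1% |
| 2% | 19.0% |
| 3% | 33.9% |
| 4% | 47.9% |
| 5% (protocol) | 60.1% |

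The probability reaches one half at a true rate of about 4.2%.

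**Effect on the primary comparison.** G1 gives 14 infants, and G2 gives 17, for power 0.90 on the rabbit data. The chance of a second event within the first 17 infants at p = 0.05 is 1 − 0.95^17 − 17 × 0.05 × 0.95^16 = 1 − 0.4181 − 0.3741 = 0.208, or 21%. At assumed rates of 2% and 3% it is 4% and 9%.

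**The case against.** A reader might infer that a harmless device would more likely than not halt this study. The documents do not support that, for two reasons.

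- **The rate.** The inference needs a true rate above about 4.2% in the enrolled infants. The 5% is for infants under 1500 g. Eligibility in F1 is 32 weeks or less, 6 to 72 hours of age, stable on bubble CPAP at no more than 8 cm H2O, and on no more than 30% oxygen. F1 explains the oxygen limit as a way to avoid evolving hyaline membrane disease. H1 names CPAP use in that disease as a main risk factor for pneumothorax. The protocol thus gives its own grounds for expecting a lower rate.
- **The counting period.** The 60% assumes the whole background risk falls after enrolment and counts. H1 sets no period for pneumothorax and omits it from the standard complications it says will be tracked for 28 days. Exposure to the device is about two hours. If only events close to the study period count, the probability falls.

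A reader might also infer that the rule endangers the primary comparison. That too goes further than the text. The sentence that stops the study also calls for an evaluation of mechanism, and attribution to the device is reviewed, so the halt may be a pause. The comparison is paired within infants, and a late halt would usually leave the 14 to 17 infants the protocol's own calculation asks for, though that calculation rests on rabbits.

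Finally, section F2 refers to a DSMB, and H2 refers to a monitoring plan attachment that is not at hand and may define the rule more fully.

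All of this limits the size and consequences of the problem. None of it reconciles 20 with 40, and the current wording of H1 would still need correcting.

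**Conclusion.** The point holds as an internal inconsistency in a decision rule, and it should be fixed. The arithmetic 1/20 = 5% is correct, but the number of infants is not the trial's. At the planned 40, the count that stops the study equals the protocol's own background rate. This also conflicts with the principle in G2 and H1 of stopping when events exceed the rate in similar patients, since 2 in 40 does not exceed 5%. These conclusions do not depend on the true rate.

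The size does. With independent infants, no device effect and all later events counted, the chance of meeting the trigger in 40 infants is 60% at the protocol's 5%, against 26% in 20. At assumed rates of 1% to 3% it is 6% to 34%, and less with a shorter counting period. The documents do not settle where in the range of about 6% to 60% the trial lies.

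**What to change.** In H1, and in the monitoring plan if it repeats the rule, reconcile the 20-infant reasoning with the 40-infant target and with the excess-over-similar-patients principle in G2 and H1. Beside the rule, state:

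- the number of infants it assumes;
- the background rate it assumes, and for which population;
- the period over which a pneumothorax counts;
- the resulting probability of a halt when the device has no effect.

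If the probability of detecting a true increase is also shown, the raised rate must be marked as an assumption. For example, at an assumed 15%, which is not in the protocol, at least two events in 40 infants would occur with probability 1 − 0.85^40 − 40 × 0.15 × 0.85^39 = 0.99. The threshold itself, including whether to keep two events, is for the safety board.

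The cost is one paragraph, agreed with the board, with no added infants or procedures. The drawbacks are that the stated false-halt figure will look less favourable than the 20-infant reasoning implies, and that if the board changes the rule a true excess might be caught slightly later.
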